### Adverse events

Information on all adverse events, such as pain, blistering, and scarring, will be collected and reported to the sponsor. Events will be analyzed by both the investigator and the sponsor and will be qualified as serious or not and related or not.

### Primary outcome measurement

The primary outcome is the disappearance of the original wart between W0 and W3. The dermatologist qualifies each wart—the original wart and the others—without knowing which one is designated by the therapist as being the original one. The study nurse then decodes which is the original wart and collects the data in the electronic case report form. At the end of the study, pictures of warts at W0 and W3 are evaluated by a blinded dermatologist using Mesurim® software to measure the mean diameter of each wart numbered and mapped. Data are recorded in a separate file with a picture code only. The percentage reduction in each wart will be calculated using the mean diameter of each wart at W0 and W3 by the data analyst.

### Secondary outcome measurements

The first secondary objective is the disappearance of all warts other than the original wart 3 weeks after the therapy. Disappearance of warts at 6 weeks will be investigated by making a telephone call to the subject. The subject’s level of belief in biofield therapy at W0 is recorded (believer, skeptical, nonbeliever).

### Data management

Data will be collected and anonymously registered using electronic case report forms in Ennov Clinical® software.

### Data monitoring

The medical procedures used in this trial comply with the most recent recommendations of the Declaration of Helsinki and French Public Health Law 2004-806 of 9 August 2004 on subject protection and safety in accordance with good clinical practice. A person mandated by the sponsor will ensure monitoring of this trial to guarantee that accurate, full, and reliable data are collected. The level of monitoring will be adapted to the low risk of the study.

At the end of the study, the data review committee, comprising the data manager, the biostatistician, and an independent dermatologist, will review all deviations from the protocol. Other members may join the committee to provide some details on the context of each deviation. The committee will qualify deviations as major or minor and shall clarify the relevance of the data with respect to these deviations: conservation of the data (for minor deviation) or exclusion of the data (for major deviation). Major deviations can affect subject safety or rights. Also, by definition, the intention-to-treat analysis requires that all data be kept for the analysis, even major deviations, except in the event of absence or withdrawal of written consent that systematically results in the exclusion of any data on the research.

### Sample size calculation

Sample size was calculated using the observed proportions method (arcsin approximation) with an open source online tool for calculating sample size by power and alpha risk. The hypothesis was that the extent of the disappearance of the original wart in the group treated by the real biofield therapist would be 70% and that it would be 30% in the group treated by the sham therapist. Indeed, it is estimated that one-third of warts resolve spontaneously within 6 months and that spontaneous regression occurs in two-thirds of cases within 2 years. Using 90% power and an alpha risk of 5%, 31 subjects are required in each group for a two-tailed proportion comparison test.

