### Eligibility

Patients with common warts on the hands or feet for at least 3 months are eligible for the study. Patients meeting one or more of the following criteria will not be included:Lack of informed consent prior to randomizationLess than 18 years old or under legal protectionTreated with oral corticotherapy for more than 6 monthsImmunosuppressed or with a history of transplant surgeryUndergoing chemotherapy or suspected to have cancerous wartsPatients with infected warts; injured warts; already treated for 90 days with chemical processes, medical devices, or surgery; or already having received biofield therapy

Subjects will be excluded from the study if their warts are treated with other treatment during the protocol. The appropriate examinations will be performed to ensure that subjects meet all the criteria. The subjects are free to leave the study at any time. Occurrence of adverse events can also lead to discontinuation.

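### The 30% sham rate at 3 weeks is supported only by 6-month and 2-year spontaneous resolution, which implies roughly 2–8% at 3 weeks; the stated 90% power therefore rests on an unsupported control rate

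*Protocol article*

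**What the plan says.** The section on sample size calculation in the protocol article assumes that disappearance of the original wart under real therapy "would be 70% and that it would be 30% in the group treated by the sham therapist". The next sentence offers the reason for the sham rate: "it is estimated that one-third of warts resolve spontaneously within 6 months", and "spontaneous regression occurs in two-thirds of cases within 2 years". No other support is given there for the 30%, and none at all for the 70%. The result is stated as "Using 90% power and an alpha risk of 5%, 31 subjects are required in each group for a two-tailed proportion comparison test", obtained by the arcsine approximation.

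The section on the primary outcome fixes the time window: "The primary outcome is the disappearance of the original wart between W0 and W3", that is, 3 weeks. The eligibility section adds that "Patients with common warts on the hands or feet for at least 3 months are eligible". The section on statistical methods names Fisher's exact test or Pearson's chi-square test for the comparison, without a rule for choosing between them.

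**The concern.** A cumulative proportion over 6 months (one-third) has been carried almost unchanged into a 3-week endpoint (30%). Three weeks is about one-ninth of 6 months, so the natural-history figures cannot by themselves yield 30%.

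The control rate is one of the two inputs to the power statement. If the sham rate is far from 30%, the stated 90% no longer describes the trial, and a reader of a null result cannot tell which effect was realistically excluded. The same holds for readers who take the section as evidence that 30% is the expected course without active treatment over 3 weeks.

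**Working it through.** **Inputs, all from the protocol article.** Rates 70% and 30%, two-sided alpha 5%, power 90%, 31 per arm, arcsine method, one-third resolved in 6 months (26 weeks) and two-thirds in 2 years (104 weeks): sample size calculation. Endpoint at 3 weeks: primary outcome measurement. Warts present for at least 3 months (13 weeks): eligibility.

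**Step 1. Reproduce the stated size.** The arcsine effect is h = 2·asin(√0.7) − 2·asin(√0.3) = 0.823. Then n = 2·((1.960 + 1.282)/0.823)² = 31.02 per arm, which agrees with 31. The pooled normal formula also gives 31. Exact power at 31 per arm for 70% versus 30% is 91.1% (chi-square) and 86.0% (Fisher).

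**Step 2. Convert the quoted natural history to 3 weeks.**

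| Shape | Formula | 3-week rate |
|---|---|---|
| Constant hazard, 6-month figure | 1 − (2/3)^(3/26) | 4.6% |
| Constant hazard, 2-year figure | 1 − (1/3)^(3/104) | 3.1% |
| Linear, 6-month figure | (1/3)·(3/26) | 3.8% |
| Linear, 2-year figure | (2/3)·(3/104) | 1.9% |
| Weibull through both points, from time 0 | shape k = ln(1.0986/0.4055)/ln 4 = 0.719; 1 − exp(−0.4055·(3/26)^0.719) | 8.2% |
| Same Weibull, wart already 13 weeks old | 1 − S(16)/S(13) | 3.9% |

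The range is 1.9% to 8.2%. At the constant hazard of the 6-month figure, 30% is reached only after 26·ln(0.7)/ln(2/3) = 22.9 weeks.

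**Step 3. Size of the gap.** 30 − 8.2 = 21.8 points and 30 − 1.9 = 28.1 points, so about 22–28 points would have to come from something other than the quoted natural history.

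**Step 4. What happens to power.** This depends on which effect is carried over to the lower sham rate. Exact power at 31 per arm with sham at 5%:

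| What is held | Real arm | Fisher | Chi-square |
|---|---|---|---|
| Real-arm rate, as stated | 70% | above 99.9% | above 99.9% |
| Difference of 40 points | 45% | 96% | 98% |
| Odds ratio (0.7/0.3)/(0.3/0.7) = 5.44 | 22% | 35% | 55% |

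The first row changes only the input under criticism. The third changes the real-arm rate as well, through an effect measure that the article does not use.

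**Step 5. What 31 per arm detects with 90% power (exact).**

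| Sham rate | Real-arm rate, chi-square | Real-arm rate, Fisher |
|---|---|---|
| 5% | 36% | 40% |
| 10% | 45% | 48% |
| 30% | 69% | 72% |

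**The case against.** *The trial is not shown to be underpowered.* A reader might infer from the time-scale mismatch that 31 per arm is too few, or that no contrast can be seen at 3 weeks. The document does not support that. It states two absolute rates and no odds ratio. Lowering the sham rate alone raises power, and so does lowering it with the 40-point difference kept. The low figures appear only under an effect measure chosen from outside the plan. This objection stands in full.

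*The conversion is not precise.* The two quoted figures do not fit one constant hazard: one-third at 6 months would give 1 − (2/3)^4 = 80% at 2 years, not two-thirds. The article also does not say whether the 6-month clock starts at wart onset, so the 3-month entry criterion cannot be used to claim that early resolvers have already left. This stands, and it is why a range is given. It does not close the gap, since the highest conversion is 8.2%.

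*The choice of test does not follow from a low sham rate.* About 1.6 sham events (0.05 × 31) might suggest that Fisher's test would be forced. The article sets no such rule, and the usual criterion uses expected counts from the pooled rate: at 5% versus 45% these are 0.25 × 31 = 7.75 per arm, so chi-square would ordinarily apply. This stands.

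*Thirty per cent is a hypothesis for a sham-treated arm, and the Background mentions a placebo effect.* That mention is general and carries no figure, and the sample size section supports the 30% with spontaneous resolution alone. A fuller rationale may exist in a document not shown, but the reason given in the article does not support the number it is attached to.

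*The 90% is already conditional on 70% versus 30%.* True, but one side of that condition is presented as supported by figures that do not support it.

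**Conclusion.** The point holds as a mismatch of time scale, not as a calculation error or a demonstrated loss of power. The quoted natural history implies roughly 2–8% disappearance at 3 weeks, against the 30% assumed. The missing 22–28 points are neither stated nor quantified as sham response.

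The range rests on simple shapes (constant hazard, linear, Weibull) fitted to the two quoted figures. All of them give less than a third of 30%. The effect on power cannot be signed, because it depends on what happens to the real-arm rate, and the 70% is itself given without support. With sham at 5% it runs from about one-third to near certainty.

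A smaller point stands beside this: even at 70% versus 30%, Fisher's test gives 86%, not 90%.

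**What to change.** In the sample size section:

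- Keep 62 subjects.
- Replace the present justification with a sham rate on the 3-week scale: natural history of about 2–8% from the quoted figures, with any placebo response added as an explicit, quantified assumption. If 30% is retained, label it an assumption.
- Restate power as what 31 per arm detects with 90% power by exact calculation: about 36% (chi-square) or 40% (Fisher) versus 5%, 45% or 48% versus 10%, and 69% or 72% versus 30%.
- Note that at 70% versus 30% power is 91% with chi-square and 86% with Fisher.

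The cost is rewording and a small table. No extra subjects are needed, and neither the design nor the analysis changes.

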### Statistical methods

Descriptive analyses with results expressed as mean and SD will be used to describe the characteristics of the participants. Categorical variables will be described as frequency and 95% CI. The primary outcome analysis will follow the intention-to-treat principle, in which all randomized patients will be analyzed in the assigned group. Both arms will be compared using Fisher’s exact test or Pearson’s chi-square test for heterogeneity analysis or Student’s *t* test accordingly. No interim analysis is anticipated. All statistical analyses will be conducted using SAS version 9.4 software (SAS Institute, Cary, NC, USA). Statistical significance will be assumed as *p* < 0.05.

### Dissemination protocol

According to the Standard Protocol Items: Recommendations for Interventional Trials (SPIRIT) guidelines, the authors declare that if the blinding is lifted, data will not be presented prior to release of the main results. The blinding will be lifted only at the end of the study. A clinical article will be written on the primary and secondary outcomes of the study. This trial is not industry-sponsored; therefore, there are no publication restrictions imposed by the funding institutional organization.

## Discussion

The goal of our study is to evaluate the efficacy of proximal therapies provided by a biofield therapist to heal cutaneous warts. The study may confirm the promising results of this treatment without furthering understanding of the mechanisms of action.

The first phase is a study protocol with a high level of evidence that could lead to strong conclusions. The main strength of the study design is that it is a single-blind, assessor-blind, placebo-controlled, randomized study.

The second phase, looking at mechanisms, will be explored only if efficacy is proven. The results of our study protocol could provide material to put forward hypotheses, to conduct new studies, and to eventually elucidate testable theories.

The biofield therapy approach to wart treatment will be discussed, as will which professionals are qualified to offer such treatment. Data derived from trials on salicylic acid and cryotherapy show only a moderate therapeutic effect [11]. Other therapies are anecdotal and could not be recommended. It may become a first-line therapy because it is less invasive than conventional treatments. To our knowledge, this is the first study to evaluate the efficacy of biofield therapy on healing cutaneous warts with a robust methodology.

### Trial status

The first participant was recruited in April 2016, and the study is currently enrolling participants. The study was expected to be completed in December 2017.

## Abbreviations

GNOMA: Groupement national pour l’organisation des médecines alternatives
SPIRIT: Standard Protocol Items: Recommendations for Interventional Trials
